## Abstract

**Background:**

Over the last years, less invasive surgical techniques with soft tissue preservation for bone conduction hearing implants (BCHI) have been introduced such as the linear incision technique combined with a punch. Results using this technique seem favorable in terms of rate of peri-abutment dermatitis (PAD), esthetics, and preservation of skin sensibility. Recently, a new standardized surgical technique for BCHI placement, the Minimally Invasive Ponto Surgery (MIPS) technique has been developed by Oticon Medical AB (Askim, Sweden). This technique aims to standardize surgery by using a novel surgical instrumentation kit and minimize soft tissue trauma.

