Although successful, the BCHI has complications. Known problems include skin inflammation, also known as peri-abutment dermatitis (PAD), pain, numbness of the skin around the implant, skin overgrowth, and implant loss [10]. PAD is graded on a five-point scale called the Holgers Index [11] and is perceived as the most common complication of BCHI use with an estimated occurrence of 16.1–38.1 % among all recipients [10]. PAD is an inflammatory process that is presumed to be multifactorial and little is known about the precise etiology of this condition [12]. Shear stress on the skin around the abutment [2, 13] sets on as the implant and abutment combination fixed to the skull is immovable. This may cause tearing of the skin (e.g., while turning on a pillow at night or during head and jaw movements). The implant and abutment are made of titanium, which may elicit a foreign body response [12, 14]. Also the formation of a biofilm on the abutment by bacteria that colonize the wound site due to persistent breach of the skin might play an important role [15, 16]. Another side effect of the BCHI is pain. This is frequently experienced by patients [17], however the exact cause for this, sometimes chronic pain, remains unknown [18–20]. Another condition which has anecdotally been observed is skin sagging, the presence of excess skin cranially to the abutment [21]. This might be problematic as it can influence the sound processor coupling and the proper function of the processor.

Various strategies for reducing complication rates with BCHIs have been employed throughout the years. Traditionally, the skin surrounding the abutment was thinned, but van de Berg et al. noted lower complication rates after BCHI surgery with a less invasive approach [20]. Since then, an even less invasive, single-stage procedure, where the soft tissue surrounding the abutment is left intact [22–25], has become one of the most common techniques used for BCHI surgery. Advantages of this tissue-preserving approach include: less surgical procedure time, reduced numbness or pain and better cosmetic results [22, 24, 25].

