### Analysis

#### Sample size calculation

The incidence of inflammation, a Holgers Index ≥ 2, between surgery and 3 months post-surgery will be compared between both groups. The sample size is calculated using the concept of effect size (ES) as presented by Lerman and Cohen [52, 53]. The proposed test concerns a two-sample test for binomial proportions, which is equivalent to a Yates corrected chi-square test for a 2 × 2 contingency table. When taking into account a type 1 error level (α) of 0.05 and a power (1-β) of 0.8, the required sample size per group is: *n = 2(zα + zβ)*
^*2*^
*/ES*
^*2*^ 
*= 2(1.65 + 0.84)*
^*2*^
*/ES*
^*2*^ 
*= 12.4/ES*
^*2*^
*.* Assuming an ES index of *medium to large* with ‘h’ of 0.65 to discriminate between two proportions, the sample size is: *n = 12.4/h*
^*2*^ 
*= 12.4/0.65*
^*2*^ 
*= 29.4*. With an expected 5 % drop-out rate, 31 participants are needed per group, resulting in a total sample size of 62 participants.

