### Protocol amendments

After initial approval (protocol version 1.2 dated 4 November 2014), the study site opened for accrual on 1 December 2014. So far, the ethics committee has approved two substantial amendments to the study protocol. In June 2015, an amendment (protocol version 1.4 12 May 2015) was approved to increase the total number of participants from 42 to 62, resulting in a decrease of the ES from 0.8 to 0.65 with 80 % power to discriminate between two proportions. In the same amendment, in order to include sufficient participants, the study was expanded from a single-center study to a multicenter study. In October 2015, the second amendment (protocol version 1.5 11 August 2015) was approved to include MIPS surgical equipment update, based on feedback after the first surgeries. The alterations in MIPS surgical package included shortening of the cannula and the addition of wings in order to increase the grip and stability of the cannula. The guide drill was also modified, resulting in a wider drilling hole making it easier to manually feel the drilling hole with the widening drill. An installation indicator was also developed, to assist in visual feedback for insertion completeness by counting the number of rotations during insertion. These updates were incorporated as MIPS became available to multiple centers around the world and surgeons provided feedback in relation to their individual outcomes. These updates are not expected to affect the primary endpoint in a significant way, hence no change in the number of participants was necessary for this amendment. The change in the surgical procedure might influence secondary outcome measures (e.g., surgery time, risks on complications such as incomplete insertion) to a limited extent. All MIPS surgeries will be analyzed as one pooled treatment group but the number of participants per MIPS version will be reported on.

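### The stated 80 % power does not belong to the Yates-corrected test that the sample size section names; that test stays below 80 % at h = 0.65, one-sided or two-sided

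*Protocol article*

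**What the plan says.** All of the following is in the protocol article.

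- Sample size calculation: the design values are introduced by "When taking into account a type 1 error level (α) of 0.05 and a power (1-β) of 0.8". The test is a two-sample binomial test, "which is equivalent to a Yates corrected chi-square test for a 2 × 2 contingency table". The formula is n = 2(zα + zβ)²/ES² with 1.65 and 0.84. The effect size is Cohen's h, described only as medium to large: "of 0.65 to discriminate between two proportions, the sample size is" 29.4 per group. An expected 5 % drop-out brings this to 31 per group, 62 in total. No control rate, MIPS rate or risk difference is given.
- Statistical analysis: the primary comparison is a chi-square test. Neither the correction nor the sidedness is mentioned.
- Protocol amendments: raising the total from 42 to 62 is described as "resulting in a decrease of the ES from 0.8 to 0.65", again with 80 % power and again without rates.
- Background: the only PAD figure in the article. PAD "is perceived as the most common complication of BCHI use with an estimated occurrence of" 16.1–38.1 % among all recipients.

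**The concern.** The sample size and the test in that paragraph do not belong together. The arcsine formula is a large-sample approximation with no continuity correction, and 1.65 is the one-sided 5 % point. A Yates correction makes the test conservative, and with few events in about 30 patients per arm the loss of power is large. The stated 80 % therefore needs checking against the named test.

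The second difficulty is that h alone tells a reader nothing about patients. The same h = 0.65 is a different absolute and relative effect at each control rate, and at a low enough control rate it cannot occur at all. The abstract describes PAD results with the control technique as favourable, so a low control rate is not far-fetched.

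At stake is how the primary result is understood. A reader who takes 80 % at face value will give a non-significant result more weight than the design can support.

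**Working it through.** **Inputs.** α = 0.05, power 0.8, z values 1.65 and 0.84, h = 0.65, 5 % drop-out and 31 per group (Sample size calculation); 1:1 allocation (Study interventions and allocation); PAD 16.1–38.1 % among all recipients (Background). Using that range as the 3-month control rate is an assumption.

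**Step 1: the plan's own figure.** 2(1.65 + 0.84)²/0.65² = 12.4/0.4225 = 29.35, which the article gives as 29.4. Then 29.35/0.95 = 30.9, so 31 per group and 62 in total. The figure reproduces, but only with a one-sided z and no correction. With a two-sided z the same formula gives 2(1.96 + 0.84)²/0.65² = 15.68/0.4225 = 37.1 per group before drop-out.

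**Step 2: what h = 0.65 means in rates.** h = 2·arcsin√p1 − 2·arcsin√p2, so p2 = sin²(arcsin√p1 − 0.325).

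- p1 = 0.161: sin²(0.4129 − 0.325) = 0.0077. PAD falls from 16.1 % to 0.8 %; relative reduction 1 − 0.0077/0.161 = 95 %.
- p1 = 0.381: sin²(0.6652 − 0.325) = 0.111. PAD falls from 38.1 % to 11.1 %; relative reduction 71 %.
- Lowest control rate at which h = 0.65 exists, with p2 = 0: sin²(0.325) = 0.102. Below 10.2 %, even zero PAD in the MIPS arm gives a smaller h.

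**Step 3: exact power at h = 0.65.** For each test, the binomial probabilities of all 2 × 2 tables in which it rejects were summed. Ranges run from 29 to 31 per arm.

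| Test at 0.05 | 16.1 % vs 0.8 % | 38.1 % vs 11.1 % |
|---|---|---|
| Yates, two-sided | 27–32 % | 57–60 % |
| Yates, one-sided | 44–50 % | 69–73 % |
| Uncorrected, two-sided | 63–67 % | 68–72 % |
| Uncorrected, one-sided | 79–82 % | 80–83 % |

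**Step 4: does this hinge on the proxy rates?** With h held at 0.65 and the control rate varied over every value at which that h is possible, the maximum Yates power (at 31 per arm) is 65 % two-sided and 74 % one-sided. The uncorrected two-sided test peaks at 74 %. Only the one-sided uncorrected test reaches 80 %.

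**Step 5: what the named test can detect with 29–31 per arm.**

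- Control rate 38.1 %: 80 % power needs a MIPS rate of at most 6.0–6.8 % (Yates two-sided) or 8.2–9.2 % (Yates one-sided).
- Control rate 16.1 %: no MIPS rate suffices. With no PAD at all under MIPS, power is 32–38 % two-sided and 51–57 % one-sided.

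**The case against.** The strongest defence is that the article never says the test is two-sided, that z = 1.65 and the directional hypothesis in the Background point to a one-sided test, and that the Statistical analysis section says only chi-square and leaves details to a later SAP. On the reading that the formula follows, one-sided and uncorrected, the stated 80 % is right. This stands, and it rules out calling the 80 % false on every reading or giving 27–60 % as the power: that range is the least favourable of four readings. It does not rescue the paragraph, which names the Yates-corrected test, and that test misses 80 % on either sidedness.

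It is also fair that 16.1–38.1 % is occurrence among all recipients. It is not specific to 3 months, to Holgers Index ≥ 2 or to the linear incision technique, and the extra consultations could raise the observed rate. At an assumed 50 % control rate, h = 0.65 would be a 61 % reduction (to 19.7 %). The reductions of 71–95 % are therefore illustrations, whereas the Yates shortfall does not depend on them.

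Finally, the Limitations section calls the small sample a major drawback, and a condensed article may leave the reasoning behind h to the full protocol. Both are true, but neither corrects the stated power.

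**Conclusion.** The point holds as an inconsistency between formula, named test and stated power. For the test named in the sample size section, power at h = 0.65 with 29–31 per arm is at most 65 % two-sided or 74 % one-sided, against the 80 % given there and repeated under Protocol amendments. This part needs no assumption about event rates.

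With the all-recipient PAD range assumed as the control rate, power is 27–60 %, 44–73 % or 63–72 % (Yates two-sided, Yates one-sided, uncorrected two-sided), and 79–83 % only for a one-sided uncorrected test.

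A reader might infer that the trial can detect only near-elimination of PAD. The article does not support that in general. It fits the 16.1 % end; at 38.1 %, h = 0.65 still leaves 11.1 % with PAD, and even the two-sided Yates test has 57–60 % power. Part of the two-sided shortfall comes from z = 1.65 rather than from the correction. The one-sided Yates figures isolate the correction, and they still fall short.

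**What to change.** Keep 62 participants and change the wording.

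1. State the sidedness, and name the same test, with or without correction, under Sample size calculation and Statistical analysis.
2. State the assumed 3-month control rate or range, with its basis, and the MIPS rate that h = 0.65 implies at it.
3. Under Sample size calculation and Protocol amendments, replace the 80 % with the exact power of the chosen test, or give the smallest difference detectable at 80 %.

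Which test to choose is partly a matter of preference. If the Yates correction is dropped to regain power, the text should note that the type 1 error of the uncorrected two-sided test can reach about 5.6 % at this sample size.

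The cost is a less favourable stated power. No extra patients or procedures are needed.

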#### Statistical analysis

This study is designed to include several endpoints including short-term results (3 months follow-up), long-term results (2 years follow-up), and an economic evaluation. Short-term results will be evaluated after all participants have reached 3 months follow-up and will describe the primary endpoint and secondary endpoints between surgery and 3 months follow-up. The primary endpoint will be described by comparing the proportions of inflammation between surgery and 3 months follow-up using a chi-square test. Long-term results will also be used for the economic analysis. Prior to analysis, a statistical analysis plan (SAP) will be created describing the method of analysis specifically for each endpoint.

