### Study interventions and allocation

All participants will undergo single-stage surgery to receive a 4-mm Ponto wide implant with mounted abutment (Oticon Medical AB, Askim, Sweden), which will be performed by an experienced ENT surgeon. Four abutment lengths are available: 6, 9, 12 and 14 mm. Subjects will be randomized to the test group (MIPS technique [26]) or the control group (linear incision technique with soft tissue preservation [24]) in the order in which they enter the study. Skin thickness is a possible factor that could influence inflammation, but this is measured during surgery, making it impossible to stratify for skin thickness prior to surgery. Considering that men are known to have significantly thicker skin than women [40], group allocation is stratified for gender. Researchers will randomize each subject using randomization software (Statistiska Konsultgruppen, Gothenburg, Sweden), which will be performed in each research center independently in a 1:1 ratio for the test and control group stratified for gender until the total number of 62 participants has been reached. Due to clear differences in surgical techniques, it is impossible to blind the surgeon, researcher or subject. In short both surgical techniques are described here:

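### The stated primary chi-square test ignores the centre and gender strata used in randomisation; it stays valid, but is conservative and may lose a few points of power if those factors are clearly prognostic

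*Protocol article*

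**What the plan says.** Under Study interventions and allocation, randomisation is "performed in each research center independently in a 1:1 ratio for the test and control group stratified for gender". The section on study design and setting lists three recruiting hospitals, one academic and two general, so there are 3 × 2 = 6 centre-by-gender cells. The reason for stratifying on gender is given in the same place: "Skin thickness is a possible factor that could influence inflammation". Skin thickness can only be measured during surgery, so gender stands in for it.

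On the analysis side, the Statistical analysis section says "The primary endpoint will be described by comparing the proportions of inflammation between surgery and 3 months follow-up using a chi-square test". The Sample size calculation describes the test as a two-sample comparison of binomial proportions, "which is equivalent to a Yates corrected chi-square test for a 2 × 2 contingency table", with "type 1 error level (α) of 0.05 and a power (1-β) of 0.8". Neither section mentions centre or gender.

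The Statistical analysis section also says that an SAP will set out the method for each endpoint before analysis. That SAP is not at hand. The article does not describe a block scheme or any other device for balancing the arms within cells.

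**The concern.** When arms are balanced within strata and the strata predict the outcome, the variation in risk between strata largely drops out of the difference between arms. A pooled 2 × 2 chi-square does not know this and still counts that variation in its standard error. The standard error is then too large, the true error rate falls below the nominal 5%, and precision gained by stratifying can be lost.

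The protocol's own reasoning makes this relevant. It stratifies on gender because it thinks skin thickness may affect inflammation, which is the primary outcome. Centre could matter too: the hospitals differ in type, the trial started in one centre and became multicentre by amendment, and grading is unblinded. With 62 participants, and a sample size that the Limitations section itself calls a major drawback, a few points of power would be worth keeping if they can be had cheaply.

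**Working it through.** **The plan's own figure.** The inputs are z values of 1.65 and 0.84 and an effect size h "of 0.65 to discriminate between two proportions". Then 2(1.65 + 0.84)² = 12.4; 12.4/0.65² = 29.35 per group; 29.35/0.95 = 30.9, so 31 per group and 62 in total. This matches "With an expected 5 % drop-out rate, 31 participants are needed per group, resulting in a total sample size of 62 participants". It assumes one unstratified table. The value 1.65 is a one-sided 5% quantile, which is why the two-sided powers below sit near 72% and not 80%. That is a separate matter.

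**Inputs from the documents.** 62 participants; six cells; 1:1 allocation; h = 0.65; control rate anchored on the Background's "estimated occurrence of 16.1–38.1 % among all recipients". I used 38.1% (the top of that range) and 25% (an assumed value inside it). The matching treated rate is sin²[(2·arcsin√p − 0.65)/2], giving 11.1% and 3.9%.

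**Assumptions, because the documents are silent.** Permuted blocks of 4 within each cell; equal numbers of men and women; centre shares of 60/20/20%, or a third each; odds ratios (OR) for gender and per step between centres, varied as in the table.

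**Size of the plain test in closed form.** With perfect balance within cells, the true variance of the difference under no treatment effect is a fraction r of what the pooled test assumes, where r = 1 − Σwₛ(pₛ − p)²/[p(1 − p)]. The two-sided size is then 2[1 − Φ(1.96/√r)]. For gender OR 3, centre OR 2 and an overall rate of 38.1%, the cell rates are 18.1, 39.9, 30.6, 57.0, 46.9 and 72.6%, with weights 0.3, 0.3, 0.1, 0.1, 0.1 and 0.1. The weighted variance is 0.0289 and p(1 − p) = 0.2358, so r = 1 − 0.0289/0.2358 = 0.877. Then 1.96/√0.877 = 2.09, and the size is 3.6%. Incomplete blocks in a trial of 62 weaken the balance slightly, so the simulated value should lie a little above this. It does.

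**Simulation.** 60,000 trials per setting, two-sided 5%, Pearson chi-square without correction against CMH on the six cells, centre shares 60/20/20%. The first figure in each size column is for a 38.1% control rate, the second for 25%.

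| Assumed strength (gender OR; centre OR per step) | Size, plain (%) | Size, CMH (%) | Power at 38.1%, plain → CMH | Power at 25%, plain → CMH |
|---|---|---|---|---|
| None (1; 1) | 5.3 / 5.0 | 5.1 / 4.9 | 72.7 → 71.5 (−1.2) | 71.4 → 69.5 (−1.9) |
| Modest (2; 1.4) | 4.9 / 4.9 | 5.0 / 5.0 | 72.9 → 72.6 (−0.3) | 71.5 → 70.3 (−1.2) |
| Moderate (3; 2) | 4.1 / 4.0 | 5.0 / 4.9 | 73.2 → 75.2 (+2.0) | 72.2 → 72.5 (+0.3) |
| Strong (5; 3) | 2.9 / 3.1 | 5.0 / 4.9 | 74.3 → 80.0 (+5.7) | 72.4 → 75.7 (+3.3) |

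With equal centre shares the picture is the same: plain size 4.7 to 4.8% (modest), 4.0 to 4.1% (moderate) and 2.8 to 3.2% (strong). The CMH power differences at 38.1% and 25% are −1.0 and −1.5 (none), −0.1 and −0.9 (modest), +2.2 and +0.7 (moderate), and +5.5 and +3.1 (strong). The Monte Carlo standard error is about 0.1 point for size, √(0.05 × 0.95/60,000), and 0.2 point for power, √(0.72 × 0.28/60,000).

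**Without balance within cells.** If nothing balances the arms within cells, the plain test's size stays at about 5% even with strongly prognostic strata. The conservatism therefore depends on the allocation scheme.

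**Continuity correction.** The Yates correction named in the sample-size section has a larger effect than the strata: with no stratum effect at all it brings the size to about 2.6 to 2.8% and two-sided power to 54 to 61%. This is a separate issue, but it bears on how the replacement test should be specified.

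**The case against.** The case against has several parts.

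- **Adjustment belongs in the SAP.** Covariate handling is commonly left there, and the article announces one. But the article does not stay silent: it names the primary test and sizes the trial on a single 2 × 2 table. The point concerns that stated choice. It stands that the unseen SAP may already resolve it.
- **The power argument is weak.** A reader might infer that the plain test loses power whenever centre or gender predicts inflammation. The calculations do not support this. At modest strength both factors are prognostic, yet CMH is level or about 1 point worse. A clear gain needs strong factors, and the documents offer no evidence of these; skin thickness is called only a possible factor, and gender is its indirect proxy. This objection stands in full.
- **The low error rate assumes within-cell balance.** Stratified 1:1 allocation suggests such balance, but no block scheme is stated. This stands as a condition on the finding.
- **Nothing is invalid.** A reader might take the mismatch to mean an unreliable p-value. The error is in the conservative direction only.
- **The remedy has its own problems.** Six cells average about 10 participants (62/6), with few events in the treated arm, so a stratified risk difference can be fragile. Stratifying on gender alone is a defensible alternative. In the 38.1%, strong-effect setting its power is 76.1%, between 74.3% (plain) and 80.0% (both factors), and its size is still only 3.5%.

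**Conclusion.** The mismatch is real and plain from the text: the trial randomises within centre and gender and then states a primary test that uses neither. Its consequence is limited. Given within-cell balance and prognostic factors, the plain test is valid but conservative, with a size of about 4.7 to 4.9%, 4% or 3% at modest, moderate or strong assumed strength. It forgoes no power at modest strength, roughly 0 to 2 points at moderate and 3 to 6 points at strong. It adds no false-positive risk and leaves the planned 62 unchanged.

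These sizes rest on assumed odds ratios, centre shares, a control rate of 38.1% or 25%, and blocks of 4. Confidence is high for the mismatch and its direction, and low for the amount. The point lies between an optional improvement and one that should be made.

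**What to change.** Before analysis, pre-specify in the SAP:

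- as primary, a CMH test without continuity correction, stratified by the randomisation factors (centre and gender);
- a Mantel-Haenszel risk difference with a 95% interval, using a variance formula suited to sparse strata;
- a sparse-cell rule fixed in advance, for example pooling the two general hospitals within gender when a cell has participants in only one arm;
- the crude chi-square as a supporting result.

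The SAP should also state how allocation was balanced within cells, so that the link between design and analysis can be checked.

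The cost is a few lines of text. Both factors are already recorded at randomisation and no extra participants are needed. The statistical downside is about 1 to 2 points of power if neither factor is prognostic, together with the thin strata that come from spreading 62 participants over six cells.
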